### Radiological parameters

Imaging will be performed using Synapse PACS and Synapse 3D (FUJIFILM Medical Systems USA, Inc.). Preoperative MRIs of all patients will be collected using contrast-enhanced T1-weighted sequences. Radiological assessment of recurrence will be performed according to the RANO (Response Assessment in Neuro-Oncology) criteria, which consider both radiological and clinical parameters:

Complete Response (CR): disappearance of all enhancing disease for at least 4 weeks, no new lesions, and stable or improved clinical status, off corticosteroids.Partial Response (PR): ≥50% decrease in the size of measurable enhancing lesions compared to baseline, sustained for at least 4 weeks, with no new lesions, stable/improved clinical condition, and stable or reduced corticosteroid use.Stable Disease (SD): radiological findings that do not meet the criteria for CR, PR, or PD, i.e., no significant tumor shrinkage or progression, with stable clinical status.Progressive Disease (PD): ≥25% increase in the size of enhancing lesions, appearance of new lesions, or clear clinical deterioration not attributable to other causes.

A local recurrence will be defined as tumor regrowth within 2 cm of the resection cavity. Residual recurrence will be defined as an increase in the residual neoplasm, while residual tumor will be defined as persistence of contrast-enhancing tumor tissue after surgery. Distant recurrence will be defined as new tumor lesions occurring >2 cm from the resection cavity. For the purpose of the binary classification framework, mixed or multifocal recurrences presenting both local progression and distant new lesions will be assimilated into the distant recurrence class.

To mitigate the inherent variability of a multicenter retrospective design, all preoperative MRIs will undergo a rigorous standardization and preprocessing pipeline prior to tumor segmentation and feature extraction. Initially, images will be subjected to N4 bias field correction to resolve magnetic field inhomogeneities. Subsequently, to ensure spatial uniformity across different scanner vendors and acquisition protocols, all scans will be co-registered to a standard anatomical space and resampled to an isotropic voxel resolution of 1x1x1 mm using appropriate interpolation techniques. Image intensity distributions will also be standardized using Z-score intensity normalization or histogram matching. Finally, to further account for residual scanner-related batch effects on the quantitative data, an advanced statistical harmonization technique, such as the ComBat method, will be applied to the extracted radiomic feature matrices prior to their integration into the machine learning classification framework.

For the development of the predictive algorithm and the automatic segmentation task, MRIs will be processed using MITK-MI brain software with the NIfTI data format. Tumor regions will be manually delineated on each slice using freehand Volume of Interest (VOI), and the software will calculate total lesion volume by summing the area of all Regions of Interest (ROIs), multiplied by slice thickness and interslice gap (Figure 3).

**Figure 3 fig3:**
[figure not shown]
Example axial post-contrast T1-weighted MRI slices of a glioblastoma patient. Left: original image with no annotation. Right: same slice with manual segmentation overlay (green) highlighting the enhancing tumor volume of interest (VOI). This illustrates the region used for subsequent feature extraction and model training.

### Outcome

#### Primary outcome

Prototype ML- and DL-based predictive prognostic models capable of forecasting the *spread of recurrence*, intended as the predicted site of recurrence relative to the original surgical cavity. In this context, *spread* refers to the spatial distribution of tumor cell regrowth—whether it occurs locally (within 2 cm or on residual tissue) or extends toward more distant brain regions. The first class is Local/Residual recurrence, defined as tumor regrowth strictly within 2 cm of the resection cavity or progressing from residual tumor tissue. The second class is Distant spread, defined as the emergence of tumor cells extending toward more distant brain regions beyond the 2 cm margin, including mixed patterns where both local and distant recurrences are simultaneously present.

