**Methods and analytics:**

A multicenter retrospective collection of clinical and radiological variables will be performed for all eligible GB patients. Variables will include demographic, surgical, pathological, and preoperative MRI features. Predictive modelling will use classical ML algorithms (e.g., Random Forest, SVM, Multilayer perceptron, etc.) and a 3D U-Net architecture for DL-based image segmentation. Dimensionality reduction (PCA, LASSO, etc.) will be used to prevent overfitting and improve model generalizability. Model performance will be assessed through Area Under the Curve (AUC), P-R curve, F-score, accuracy, sensitivity, specificity, confusion matrix, and Dice score for segmentation.

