**Discussion:**

The development of Artificial Intelligence (AI)-based predictive models for GB is expected to provide a major contribution to outcome prediction, early targeted interventions, and personalized care. These tools may support optimized resource allocation, reduce healthcare costs, and improve patient and family outcomes. The findings from this study will serve as a foundation for a future prospective multicenter validation study.

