**Figure 1 fig1:**
[figure not shown]
Gantt chart outlining the 24-month project timeline and task allocation. Key activities include: administrative and ethics clearance; research training; retrospective data collection; definition of prognostic parameters and data-management protocols; software system design; development and validation of manual and semi-automated MRI segmentation tools; implementation of Machine Learning and Deep Learning classification frameworks; statistical integration of methods; overall analysis, manuscript drafting, and result dissemination; and recurring project meetings. Colour coding denotes responsibility: grey bars indicate tasks conducted by all partners, orange bars those led by the computer science centres, and blue bars those led by the medical centres.

From month 7 through month 24, the focus shifts to development, integration and validation of the prototype ML- and DL-based predictive prognostic models. Retrospective data will be used to train separate ML and DL models aimed at predicting the spread of GB recurrence. These models will be refined iteratively and integrated into a unified framework of prototype ML- and DL-based predictive prognostic models, which will then be applied to prospective data as it becomes available.

Concurrently, an automated segmentation software prototype will be deployed and optimized throughout this period. All software components, from preprocessing pipelines to the predictive prognostic models and segmentation modules, will undergo continuous testing and improvement.

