Classification of the extracted feature vectors will be carried out using conventional feed-forward Artificial Neural Networks, Support Vector Machines (SVM), Decision trees, Multi layer perceptron (MLP) (10, 11, 16–18) and other established classification algorithms (19). To enhance predictive performance, ensemble learning methods such as Random Forests will also be explored.

To ensure a robust evaluation and mitigate the risk of optimistic performance estimates, model validation will be conducted using a nested repeated stratified k-fold cross-validation framework. This rigorous approach prevents data leakage by explicitly separating hyperparameter optimization, which is executed using grid search or randomized search within the inner cross-validation loop, from the final unbiased performance assessment conducted on the hold-out folds in the outer loop. Crucially, to preserve the strict separation between training and testing cohorts, all data transformation procedures, including dimensionality reduction, feature selection, and the application of data augmentation techniques such as SMOTE, will be fitted exclusively on the training folds and subsequently applied to the corresponding independent validation folds. Model performance will be assessed using Receiver Operating Characteristic (ROC) curves, along with sensitivity and specificity metrics (Figure 4).

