## Conclusion

AI-based predictive algorithms are expected to make a substantial contribution to accurate outcome prediction, early targeted interventions, and personalized management of patients with GB. In particular, the development of ML- and DL-based models to identify prognostic patterns, such as the spread of recurrence, represents an exploratory step toward understanding glioblastoma spatial behavior. While these computational tools hold promise, their actual clinical utility, their impact on patient outcomes, and their potential for guiding targeted interventions remain to be rigorously evaluated in future prospective, clinically validated trials. Our experience suggests the potential for ML in identifying recurrence patterns in the data for therapeutic improvement and optimize care pathways. This work represents a further step toward the implementation of precision medicine in the management of GB.

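### The primary outcome is a deliverable, not a measured quantity, so *capable* cannot be tested and a near-chance result would not count against it

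*Protocol article*

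**What the plan says.** The Primary outcome section of the protocol article opens with "Prototype ML- and DL-based predictive prognostic models capable of forecasting the" spread of recurrence. It then defines two classes. One is local/residual: "The first class is Local/Residual recurrence, defined as tumor regrowth strictly within 2 cm of the resection cavity or progressing from residual tumor tissue". The other is distant spread, which includes mixed patterns. The section contains no performance measure, reference value or comparator.

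Performance measures appear elsewhere. The Abstract (Methods and analytics) says: "Model performance will be assessed through Area Under the Curve (AUC), P-R curve, F-score, accuracy, sensitivity, specificity, confusion matrix". The Analysis section gives a shorter list: "Model performance will be assessed using Receiver Operating Characteristic (ROC) curves, along with sensitivity and specificity metrics". It also fixes the validation design: "model validation will be conducted using a nested repeated stratified k-fold cross-validation framework". Neither list marks a measure as primary or connects it to the primary outcome. The Analysis section makes classical machine learning the primary framework and treats deep-learning classification as an exploratory secondary analysis.

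On the next step, the Study design section (text after Figure 1) says the models will be integrated into one framework, "which will then be applied to prospective data as it becomes available". The Abstract (Discussion) adds: "The findings from this study will serve as a foundation for a future prospective multicenter validation study". Neither statement carries a performance condition.

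**The concern.** A primary outcome should be something the data can answer. Here it is an object to be built, qualified by one word, *capable*, that nothing in the document defines. The planned performance results sit beside the outcome and do not enter it, so no stated result would lead the investigators to conclude that the outcome was not achieved.

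Two features make this matter. First, the Analysis section names several classifiers and several dimension-reduction methods, and the two lists of measures differ. Without a lead measure for a lead pipeline, the most favourable combination can be put forward afterwards. Second, the move to prospective data is written as the next scheduled activity, so a model with no signal would take the same path as a useful one.

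**Working it through.** **1. The plan's own figure.** Study population and sample size: about 200 patients screened, about 30% excluded. 200 × (1 − 0.30) = 140, as stated. No target AUC, error rate or success threshold is given, so there is nothing further to reproduce.

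**2. The text, side by side.**

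| Place | What it fixes | What it does not fix |
|---|---|---|
| Primary outcome | A product and two classes | A measure, reference value or meaning for *capable* |
| Abstract; Analysis | Measures and nested cross-validation | Which measure is primary; any link to the outcome |
| Study design; Abstract (Discussion) | Application to prospective data; later validation study | Any dependence on performance |

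The point rests on this comparison. The figures below only show its size.

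**3. Assumptions for the illustration.** The document calls distant recurrence rarer but gives no share. I take 10%, 20% and 30% of 140, that is m = 14, 28 and 42 distant cases against n = 126, 112 and 98 local/residual. The AUC is treated as coming from 140 independent predictions. The extra variance of repeated cross-validation is ignored.

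**4. What chance alone can produce.** With no signal, SE₀ = √[(m + n + 1)/(12mn)].

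- 10%: √[141/(12 × 14 × 126)] = 0.082; 95% range 0.34 to 0.66
- 20%: √[141/(12 × 28 × 112)] = 0.061; 95% range 0.38 to 0.62
- 30%: √[141/(12 × 42 × 98)] = 0.053; 95% range 0.395 to 0.605

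One no-signal model reaches an AUC of 0.60 or more with probability p of about 0.11, 0.05 and 0.03. For the best of five independent models the probability is 1 − (1 − p)⁵. A simulation of 20,000 draws gave 0.44, 0.23 and 0.14, and for the best of ten 0.68, 0.41 and 0.27. Classifiers trained on the same patients are correlated, so the true figures would be lower.

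**5. What a testable criterion would do.** Suppose the lower 95% limit of the outer-fold AUC must exceed 0.5. With the Hanley-McNeil standard error, SE(A)² = [A(1 − A) + (m − 1)(Q₁ − A²) + (n − 1)(Q₂ − A²)]/(mn), where Q₁ = A/(2 − A) and Q₂ = 2A²/(1 + A). Power is approximated by Φ[(A − 0.5 − 1.96 SE₀)/SE(A)].

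Worked case, 10% distant and A = 0.70: Q₁ = 0.538, Q₂ = 0.576, and SE² = (0.21 + 13 × 0.0485 + 125 × 0.0865)/1764 = 0.0066, so SE = 0.081. Power = Φ[(0.20 − 0.160)/0.081] = 0.69.

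| Distant share | Smallest AUC that qualifies | Power at AUC 0.70 | Missed |
|---|---|---|---|
| 10% | 0.665 | 69% | 31% |
| 20% | 0.625 | 91% | 9% |
| 30% | 0.605 | 97% | 3% |

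In a separate simulation (4,000 binormal datasets per setting, DeLong limits) the criterion was met in about 3% of datasets with no signal. That rate holds for a single prespecified procedure only.

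**The case against.** The strongest reply is that performance will be measured, and measured well. Nested cross-validation with held-out outer folds is planned, and a null model would show an AUC near 0.5. A reader might infer from the outcome wording that the study cannot return a negative answer; the Analysis section does not support that. A reader might also infer that the outcome is met with certainty whatever happens. That ignores the word *capable*, which in ordinary reading a chance-level classifier would not satisfy. The defect is that the word has no criterion.

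Nor do the documents support reading the prospective step as clinical use. It is application to new data, followed by a validation study, and the Conclusion says clinical utility and impact on outcomes "remain to be rigorously evaluated in future prospective, clinically validated trials". Prospective application could itself expose a null model.

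A further tempting argument is that calling every patient local would pass on accuracy. No section sets an accuracy threshold, and such a rule has zero sensitivity for distant spread, which the planned measures would reveal.

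It is also fair that an article may leave intervals and reference values to a fuller document, and that an exploratory study need not have a pass/fail rule. This reduces the point but does not remove it. The article does state the primary outcome, in its own section, and states it as a product. An analysis plan can add detail to a quantity, but here it has been given none.

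**Conclusion.** The point holds as a badly fixed primary outcome. The protocol article names a deliverable, leaves *capable* without a test, ties none of its performance measures to the outcome, and lets the prospective step proceed independently of the result. A near-chance result would be seen but would not count against the primary outcome, and selective emphasis among classifiers and metrics is left open.

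This conclusion rests on the text alone. The size of the room for a chance finding (0.44 to 0.14 for the best of five at AUC 0.60) depends on the assumed distant share of 10% to 30% and on independence between models, so it is an upper illustration. The consequence is for how the study's claim can be interpreted; no harm to patients is shown. The change should be made, but the study is not invalid without it.

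**What to change.** Restate the primary outcome as the outer-fold AUC for distant versus local/residual recurrence of one prespecified classical-ML pipeline. Any choice among classifiers and dimension-reduction methods should be made inside the inner loop, so that the outer-fold result belongs to a single procedure. Report it with a patient-level 95% CI that allows for the repeated cross-validation.

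State that the models will be described as capable of forecasting spread only if the lower limit exceeds 0.5. Otherwise, report that predictive ability was not shown, and say so explicitly if the models are still applied to prospective data. Keep the prototypes and the segmentation software as deliverables.

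The cost is protocol wording and one interval. Nested cross-validation and the primacy of classical ML are already planned, and no extra patients or data are needed. The downside is that the study can then miss its primary outcome despite real signal, at the rates tabulated above. These should be acknowledged in the protocol, along with the distant share once it is known.

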#### Secondary outcome

Development of a software system for (semi) automatic segmentation and volume measurement in MRIs.

### Analysis

Data analysis will be performed using ML and DL techniques, both of which fall under the broader field of AI and supervised pattern recognition (10, 11).

ML is a well-established approach that involves algorithms capable of processing and learning from data without being explicitly programmed. Once trained, these algorithms can apply the learned patterns to make data-driven predictions. A typical ML workflow includes several sequential stages: data acquisition and preprocessing, computation of a large number of variables (also referred to as features or attributes, which may be either domain-specific or domain-agnostic), dimensionality reduction, model training and validation, and eventual deployment (12). During training, the ML model identifies patterns and correlations between features and the outcome variable of interest, aiming to generalize this knowledge and accurately predict outcomes even in previously unseen cases.

DL represents a more recent advancement within ML, offering a key advantage in its ability to automatically learn complex, high-level features directly from the data. Unlike traditional ML approaches, which require manual feature engineering by domain experts or extensive trial-and-error processes, DL models progressively extract informative representations in an automated and hierarchical manner. This significantly reduces the dependency on prior domain knowledge and manual intervention in feature selection.

The goal of the ML and DL classification approaches will be to predict the spread of GB recurrence, based on preoperative clinical, radiological, and instrumental data. These models aim to classify patients according to expected recurrence patterns, such as local versus distant regrowth, and provide spatial forecasts that can support surgical planning and treatment personalization.

Data analysis will be conducted using Python and Matlab environments. The computational framework will rely on the integrated and multivariate analysis of features derived from both clinical and imaging data collected during the pre-operative periods.

For MRI image analysis, feature extraction will be performed using the open-source PyRadiomics library, in strict compliance with the Image Biomarker Standardisation Initiative (IBSI) guidelines. To ensure standardization, all images will be resampled to an isotropic voxel size of 1x1x1 mm using B-spline interpolation prior to extraction. Image discretization will be performed using a fixed bin width approach to maintain the absolute intensity meaning of the MRI sequences. The extracted agnostic radiomic features will encompass multiple categories, including 3D shape, first-order statistics, and higher-order texture matrices such as the Gray Level Co-occurrence Matrix (GLCM), Gray Level Run Length Matrix (GLRLM), Gray Level Size Zone Matrix (GLSZM), Gray Level Dependence Matrix (GLDM), and Neighborhood Gray Tone Difference Matrix (NGTDM). To guarantee methodological robustness and address segmentation uncertainty, a reproducibility analysis will be conducted. A representative subset of cases will be independently segmented by two different expert radiologists. The Intra-class Correlation Coefficient (ICC) will be calculated for each extracted feature, and only robust features demonstrating an ICC greater than 0.75 will be retained for the dimensionality reduction and ML modeling phases. To strictly prevent any circular dependency within the study design, the radiomic feature extraction for the predictive classification models will rely exclusively on the manual segmentations performed by the expert neuroradiologists, which serve as the definitive ground truth. The development of the 3D U-Net is designated as a parallel and independent task. The automated segmentation tool will be trained on these manual annotations but will not be utilized to generate the input features for the retrospective predictive models, positioning it solely as a standalone secondary outcome for future prospective applications.

The issue of class imbalance, which may be present in the dataset, will be addressed by incorporating appropriate strategies during model training. Depending on the observed distribution, techniques such as class weighting or resampling (e.g., oversampling the minority class) may be applied to reduce potential bias and improve the model’s ability to detect less represented cases.

After the contouring and segmentation steps, a set of feature descriptors will be extracted from the segmented volumes of interest to enable supervised pattern recognition using ML techniques. Initially, expert radiologists will manually perform the segmentation process. However, as the study progresses, we will also develop a semiautomatic segmentation tool designed to support and streamline the radiologists’ workflow.

In the ML-based analysis, the extracted features will include a combination of specific clinical variables (as detailed in the “Data Collection” and “Radiological Parameters” sections), semantic descriptors derived from diagnostic imaging, and agnostic radiomic features that are independent of anatomical context (13).

Once the clinical and imaging feature vectors are defined, the resulting dataset will contain a large number of variables relative to the number of cases available. This imbalance may lead to what is commonly referred to as the “curse of dimensionality,” a situation in which the high dimensionality of the data reduces classification performance. This occurs because the number of samples required to accurately estimate complex relationships grows exponentially with the number of features.

To mitigate this issue, a dimensionality reduction step will be incorporated. This step will eliminate redundant or irrelevant features and retain only the most informative variables, thereby enhancing both model performance and computational efficiency (14). We will employ feature extraction techniques such as Principal Component Analysis (PCA), Independent Component Analysis (ICA), and Fisher Linear Discriminant Analysis (FLDA), which generate new, reduced-dimensional feature sets from the original data. In parallel, we will apply feature selection methods aimed at identifying a subset of the most predictive features while discarding those that do not contribute meaningfully to classification accuracy.

An added benefit of feature selection lies in improving the interpretability of ML models. By isolating the most relevant features, the process supports human-understandable insights into the decision-making process and helps reduce the so-called “black box” nature often associated with ML algorithms, thus contributing to model explainability (15).

Classification of the extracted feature vectors will be carried out using conventional feed-forward Artificial Neural Networks, Support Vector Machines (SVM), Decision trees, Multi layer perceptron (MLP) (10, 11, 16–18) and other established classification algorithms (19). To enhance predictive performance, ensemble learning methods such as Random Forests will also be explored.

To ensure a robust evaluation and mitigate the risk of optimistic performance estimates, model validation will be conducted using a nested repeated stratified k-fold cross-validation framework. This rigorous approach prevents data leakage by explicitly separating hyperparameter optimization, which is executed using grid search or randomized search within the inner cross-validation loop, from the final unbiased performance assessment conducted on the hold-out folds in the outer loop. Crucially, to preserve the strict separation between training and testing cohorts, all data transformation procedures, including dimensionality reduction, feature selection, and the application of data augmentation techniques such as SMOTE, will be fitted exclusively on the training folds and subsequently applied to the corresponding independent validation folds. Model performance will be assessed using Receiver Operating Characteristic (ROC) curves, along with sensitivity and specificity metrics (Figure 4).

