### Data collection

For each enrolled patient, we will extract clinical and imaging parameters from electronic medical records. Demographic and clinical variables will include age, tumor localization and laterality, presence of residual tumor after surgery, type of adjuvant treatment, type of recurrence (local or residual, distant, or combination), delay of relapse and biomolecular markers of the tumor.

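### The clinical inputs are defined by a list with at least three variables not known before surgery, although the models are described as preoperative

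*Protocol article*

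**What the plan says.** The Analysis section of the protocol article defines the clinical inputs by cross-reference: "the extracted features will include a combination of specific clinical variables", for which it points to the Data collection and Radiological parameters sections. No listed variable is excluded there or elsewhere.

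The Data collection section names "age, tumor localization and laterality, presence of residual tumor after surgery, type of adjuvant treatment" and then "type of recurrence (local or residual, distant, or combination), delay of relapse and biomolecular markers of the tumor".

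The same Analysis section says that prediction will be "based on preoperative clinical, radiological, and instrumental data". It repeats the restriction when it describes the computational framework, and it gives surgical planning as one use of the output. The Introduction also argues that a forecast made in advance could shape the first resection.

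The Primary outcome section defines two classes. The first is regrowth "strictly within 2 cm of the resection cavity or progressing from residual tumor tissue". The second is distant spread, with mixed patterns assigned to it.

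Against leakage, the Analysis section provides nested, repeated, stratified cross-validation, with dimensionality reduction, feature selection and oversampling fitted on training folds only.

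**The concern.** A model to be used before an operation may use only what is known before it. The cross-reference admits variables that arise at surgery, after it, or only when the tumour returns.

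Time to relapse is the plainest case, because it does not exist until the outcome has occurred. Residual tumour is different: it precedes recurrence, but regrowth from residual tissue is one route into the first class, so as a predictor it is structurally linked to the outcome.

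The stakes are the primary result. Classical machine learning on these features is named as the primary framework. If later variables enter, the cross-validated AUC describes prediction with information the surgeon will not have, and the model cannot be run at the surgical decision point. The planned feature-selection step keeps the most informative variables, so it would tend to retain such items rather than drop them.

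**Working it through.** **The plan's own figure.** About 200 screened patients less 30% gives 200 × (1 − 0.30) = 140, the stated cohort. This reproduces. The point does not depend on it; 140 serves only as the sample size of the illustration below.

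**Classifying the list.** Each item in Data collection is set against the preoperative time point, with localization and laterality counted as one item:

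| Item | Known before surgery? |
|---|---|
| Age | Yes |
| Localization and laterality | Yes |
| Residual tumour after surgery | No |
| Adjuvant treatment | No |
| Delay of relapse | No, known only at recurrence |
| Biomolecular markers | Probably not; timing not stated |
| Type of recurrence | No; this is the outcome |

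The count is 2 preoperative + 3 clearly later + 1 probably later + 1 label = 7. The entry for markers is an inference: they need tissue, and Study population and sample size excludes needle biopsies, so the tissue would come from the resection.

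**Do other passages remove the conflict?**

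- The Abstract lists surgical and pathological variables beside preoperative MRI features and then turns to modelling. This does not confine the inputs to preoperative data.
- The fold-wise safeguard governs how transformations are estimated. A late variable is recorded for training and test patients alike, so it passes through unchanged.
- The separate safeguard against circularity concerns the automated segmentation tool, not the clinical inputs.

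**Illustration of size (assumed inputs).** The document gives neither the share of distant recurrences nor the rate of residual tumour by class. For a single yes/no predictor, AUC = 0.5 + (p_local − p_distant)/2, where p is the share of patients with residual tumour in each class.

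- Difference of 0: AUC = 0.50.
- Difference of 10 points: 0.5 + 0.10/2 = 0.55.
- Difference of 30 points (60% against 30%): 0.5 + 0.30/2 = 0.65.

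The last case was also simulated with 140 patients, ten pure-noise preoperative features, ridge logistic regression, five-fold stratified cross-validation and 100 repeats:

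| Assumed distant share | AUC, noise only | AUC, noise + residual tumour |
|---|---|---|
| 10% | 0.496 | 0.594 |
| 20% | 0.510 | 0.603 |
| 30% | 0.500 | 0.615 |

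Under these assumptions, one postoperative variable moves a model with no preoperative signal from about 0.50 to about 0.59–0.62. Time to relapse was not simulated, because the document gives no basis for its relation to the class.

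**The case against.** The strongest reply is that Data collection is an extraction list, and a retrospective extraction list must contain the outcome and follow-up items. The reference to specific variables can mean a selection, and the preoperative limit, stated twice, tells the reader which to select. A closed predictor list is also something an article may leave to a fuller plan.

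Part of this stands. A reader might infer that the model would predict from its own label and reach an AUC of 1.0 by construction. The documents do not support that: the Primary outcome section makes recurrence type the thing to be predicted, and the Analysis section distinguishes features from the outcome variable. A simulation that enters recurrence type does return 1.00, but this shows only that a label predicts itself. Nor do the documents make RANO response an input. It is used to assess recurrence, and the Radiological parameters section also holds plausible inputs such as preoperative MRI and lesion volume.

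Two further limits are fair. Residual tumour does not determine the class, since a patient with residual tumour and a mixed pattern is counted as distant. And the article also names radiotherapy planning and later oncological treatment as uses, for which residual status or markers could be available.

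The reply does not remove the conflict over residual tumour, adjuvant treatment and time to relapse. No sentence excludes them, and the Abstract points towards wider inputs. This is a contradiction between two statements in the article, not a detail left out.

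**Conclusion.** The point holds as an internal contradiction. The clinical inputs are taken without restriction from a list in which three of seven items are clearly unknown before surgery, while the models are described as preoperative and meant for surgical planning. The number rises to four if markers come from resected tissue, which is likely but not stated. Recurrence type is on the same list; it is evidently the label, and the text should say so.

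If the cross-reference is followed as written, the primary AUC would not describe preoperative performance and the model could not serve its surgical use. The size of any inflation cannot be derived from the document. The rise to 0.59–0.62 from residual tumour alone rests on assumed rates of 60% and 30% and on otherwise uninformative features.

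**What to change.** In the Analysis section, replace the cross-reference with a stated set of inputs and say when each becomes available:

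- **Primary model:** only variables known before surgery, namely age, localization, laterality, and semantic and radiomic features from preoperative MRI.
- **Label:** state that recurrence type is the outcome only.
- **Never inputs:** time to relapse and any assessment of recurrence.
- **Optional second model:** if residual tumour, adjuvant treatment or tissue-based markers are of interest, fit a separately named postoperative model, report it apart, and make no surgical-planning claim from it.

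The change needs wording only; no data collection is lost, since the items can still be extracted. The downside is a possibly lower AUC for the primary model, but one that applies at the time of intended use.
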